## Abstract

**Background:**

The stellate ganglion block (SGB) can lead to vasodilation of the head and neck. However, controversy remains concerning the changes in extracerebral blood flow. The objective of this study is to assess the effects of SGB on the blood flow to the neck.

**Methods:**

A randomized controlled crossover trial with 38 participants will be conducted. Participants who have primary headaches will be assigned to either group A or B. Patients in group A will receive SGB with 6 ml 1% lidocaine, and after a one-week washout period, they will undergo the second SGB with 6 ml normal saline. In contrast, patients in group B will receive the opposite protocol. Data will be collected at baseline (T0) and at 15 min after the first intervention (T1), 15 min before the second intervention (T2), 15 min after the second intervention (T3) and at a 3-week follow up (T4). T1 is the primary time point for the primary outcome analysis. The primary outcomes include the peak systolic velocity (PSV), the end diastolic velocity (EDV), resistance index (RI) and vessel diameter of the common carotid artery (CCA) and vertebral artery (VA). The secondary outcomes include the rate of ptosis, the rate of conjunctival flushing, and the numerical rating scale (NRS) pain score. Additionally, adverse events (AEs) or serious adverse events (SAEs) will be collected at each assessment point.

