### Trial design

A double-blinded, randomized controlled crossover trial will be conducted, and all subjects will undergo ultrasound-guided SBG. Group A will first undergo SGB with 6 ml 1% lidocaine. After a one-week washout period, this group will receive ultrasound-guided SGB with 6 ml normal saline. In contrast, group B will receive the opposite protocol. That is, group B subjects will first receive SGB with 6 ml normal saline, and after a one-week washout period, this group will receive SGB with 6 ml 1% lidocaine.

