### Outcomes

#### Primary outcomes

To evaluate the effect of SGB on the vascular blood flow in the neck, the primary outcomes will be the peak systolic velocity (PSV), the end diastolic velocity (EDV), diameter, and resistance index (RI) of the CCA and VA at 15 min after the first SGB (T1). Sonograms will be obtained with a Mylab 90 (Genova, Italy) by using a 4–10-MHz linear transducer. For flow-volume measurements, a straight segment of the common carotid artery at least 2 cm below the carotid bulb will be selected [24].

All measurements will be performed by an ultrasound specialist using the same ultrasound instrument.

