#### Secondary outcomes

Secondary outcomes include: (1) the PSV, EDV, RI, and diameter of the CCA and VA at T0, T2, T3, and T4; (2) the rate of ptosis and conjunctival flushing at T1 and T3 (ptosis and conjunctival flushing are considered the standard indicators of SGB of success [25]); (3) the numerical rating scale (NRS) at T0 and T4. The NRS allows the patient to describe the intensity of his/her pain as a number, usually ranging from 0 to 10, where 0 means no pain and 10 means pain as “bad as it could be” [26].

Adverse events (AEs) or serious adverse events (SAEs) will be collected at each assessment time point and any AEs or SAEs related to the intervention will be reported. For an overview of the schedule of enrolment, interventions, and assessments please see Fig. 2.

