### Sample size

The sample size was calculated based on the CCA blood flow results reported previously [11]. With an expected difference of 10 cm/s in peak systolic velocity of the CCA between group means, an SD of 10 cm/s, α = 0.05, and β = 0.8, a sample size of 17 patients was required in each group. To compensate for a dropout rate of up to 10%, we will enrol a total of 38 cases (19 for each group) for this study. Although the study is powered to allow a 15% dropout rate, we will make every effort to minimise patient loss and missing data during the trial period.

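### The trial is run as a two-period crossover, but its primary outcome and sample size use the first period only, so the primary answer is less precise than the collected data allow

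*Protocol article*

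**What the plan says.** Trial design in the protocol article reads: "A double-blinded, randomized controlled crossover trial will be conducted, and all subjects will undergo ultrasound-guided SBG". One group receives lidocaine then saline, the other the reverse, one week apart. The Objective section has flow measured before and 15 minutes after each procedure.

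The primary outcome is narrower. The Abstract says "T1 is the primary time point for the primary outcome analysis". Primary outcomes lists peak systolic velocity (PSV), end diastolic velocity, diameter and "resistance index (RI) of the CCA and VA at 15 min after the first SGB (T1"). Secondary outcomes takes the remaining flow readings: "the PSV, EDV, RI, and diameter of the CCA and VA at T0, T2, T3, and T4".

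Sample size starts "With an expected difference of 10 cm/s in peak systolic velocity of the CCA between group means", takes an SD of 10 cm/s with "α = 0.05, and β = 0.8", and concludes that "a sample size of 17 patients was required in each group". It gives no within-patient SD or correlation.

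Statistical analyses names a two-way 2 × 4 ANOVA with Tukey tests for parametric data, and Friedman then Wilcoxon tests otherwise. It does not name the ANOVA factors, although there are five time points (T0 to T4). It also says that a statistical analysis plan will be written before the data are analysed.

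**The concern.** A crossover is run so that each patient serves as their own control. Here T1 holds lidocaine readings from one set of patients and saline readings from another. Variation between patients, who may be aged 18 to 70, therefore stays in the error of the primary comparison. T3 is the matching reading after the other injection and would allow the within-patient contrast, but it is secondary.

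Every patient undergoes a second neck injection, with the risks set out under Expected risks, and that injection adds nothing to the primary answer. What is at stake is the width of the primary confidence interval and the consistency of the design, primary outcome, sample size and named model.

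**Working it through.** **Inputs.** From Sample size: difference 10 cm/s in PSV of the common carotid artery, SD 10 cm/s, α 0.05 (taken as two-sided), 17 per group, 10% dropout, 38 enrolled. The printed β of 0.8 is read as power 0.80. The correlation ρ between readings in the same patient is not given; I assume 0.3, 0.5 and 0.7, with 0 as the floor.

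**Step 1: reproduce the plan's figure.** For two independent groups, the normal approximation gives n = 2(1.96 + 0.842)² × (10/10)² = 15.7, so 16 per group. The exact two-sample t-test has power 0.781 at 16 and 0.807 at 17, so it needs 17. Then 17/0.90 = 18.9, so 19 per group and 38 in total. The stated figures reproduce as a parallel-group calculation with no within-patient term.

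**Step 2: precision with 34 completers.**

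- T1 only, 17 versus 17: SE = 10 × √(2/17) = 3.43 cm/s.
- T1 versus T3 within patients: SE = 10 × √(2(1 − ρ)/34).
- Ratio of the two: √(2/(1 − ρ)).

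| ρ | SE, T1 only | SE, T1 versus T3 | Ratio | Difference detectable with 80% power, T1 only | Same, T1 versus T3 |
|---|---|---|---|---|---|
| 0 | 3.43 | 2.43 | 1.4 | 9.9 | 7.0 |
| 0.3 | 3.43 | 2.03 | 1.7 | 9.9 | 5.9 |
| 0.5 | 3.43 | 1.71 | 2.0 | 9.9 | 5.0 |
| 0.7 | 3.43 | 1.33 | 2.6 | 9.9 | 3.8 |

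Both analyses have 32 degrees of freedom, so the SE ratio is also the ratio of interval widths.

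**Step 3: T1 adjusted for T0.** SE = 3.43 × √(1 − ρ²), with 31 degrees of freedom and ρ now the T0–T1 correlation. This gives 3.27, 2.97 and 2.45 cm/s at ρ = 0.3, 0.5 and 0.7. Power for 10 cm/s is 84%, 90% and 98%, against 81% unadjusted.

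**Step 4: how the baselines enter.** The crossover SEs in Step 2 use T1 and T3 alone. If change scores (T1 − T0 and T3 − T2) were contrasted instead, and all four readings were equally correlated, SE = 10 × √(4(1 − ρ)/34) = 2.87, 2.43 and 1.88 cm/s. The ratio to the T1-only SE then drops to 1.2, 1.4 and 1.8. The loss is smaller if same-day readings correlate more strongly than readings a week apart, but the documents give no figure for either.

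**Step 5: does the named ANOVA settle it?** If its four levels are time points, second-period readings could enter the model, but that would not fit a primary outcome fixed at T1. If it covers something else, it does not describe the T1 comparison. It states no period, sequence or within-patient treatment term. On either reading, Statistical analyses and Primary outcomes need to be reconciled.

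**The case against.** The strongest reply is that a first-period comparison is a legitimate randomised contrast. It cannot be affected by carry-over, and on the plan's own inputs it has 81% power with 17 per group. That stands: the primary test is neither biased nor underpowered for 10 cm/s.

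A reader might infer that the T1 values will be compared raw, with each patient's baseline ignored. The documents do not say so. The Abstract calls T0 the baseline, listing T0 among secondary outcomes does not bar its use as a covariate, and adjustment may be left to the statistical analysis plan. Nor is the second period discarded: T2 and T3 are collected and are named secondary flow outcomes. Chance imbalance at T0 is sampling error already reflected in the standard error, not bias.

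It is also tempting to quote power for a smaller effect, such as 5 cm/s. The documents name no such effect, so the case should not rest on it.

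Finally, changing a registered primary outcome late in recruitment has a real cost. Trial status reports 27 of 38 participants enrolled by 12 October 2017.

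None of this removes the narrow point. The choice of primary reading is made in the protocol, it excludes the second period, and the article gives no reason, such as avoiding carry-over, for that choice.

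**Conclusion.** The point holds as a loss of efficiency and an inconsistency between design, primary outcome, sample size and named model. It does not show an invalid analysis or a wrong sample size. The primary interval is 1.7 to 2.6 times wider than a T1 versus T3 contrast would give at assumed correlations of 0.3 to 0.7, and 1.4 times wider even at zero. These figures assume SD 10 cm/s at both readings, 34 completers, negligible carry-over and no use of baselines. The direction holds at any non-negative correlation; the exact size depends on a correlation that the documents do not give. This should be fixed, but the trial can answer its stated question without the change.

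**What to change.** Before unblinding, amend the primary analysis to the within-patient lidocaine-minus-saline difference 15 minutes after injection, from T1 and T3. Use a crossover model with period and sequence terms, and enter T0 and T2 as covariates rather than taking simple change scores, which can lose much of the gain (Step 4). State the factors of the model so that it agrees with the primary outcome.

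Keep the T1 comparison, adjusted for T0 by ANCOVA, as a prespecified sensitivity analysis. Report it whatever T2 shows: a carry-over test has little power at this size and should not decide which analysis counts. If the sponsor prefers to keep T1 as primary, adjust it for T0 and state why the second period is left out.

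**Cost.** No extra patient, visit or scan is needed, because Data collection process already schedules T0 to T3. The article plans no interim analysis, and the statistical analysis plan was still to be written. The price is a protocol and registry amendment late in recruitment, and an estimate that assumes negligible carry-over of flow effects at one week.

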**Discussion:**

This study will comprehensively investigate the efficacy of SGB in extracerebral blood flow. Our research may also suggest that SGB will be effective in reducing pain in patients with primary headaches.

**Trial registration:**

Chinese Clinical Trial Registry, identifier ChiCTR-IOR-17011536. Registered on 1 June 2017.

**Electronic supplementary material:**

The online version of this article (10.1186/s13063-018-2736-y) contains supplementary material, which is available to authorized users.

## Background

The stellate ganglion measures approximately 2.5 cm in length, 1 cm in width, and 0.5 cm in thickness. It is located posteriorly in the chest, in front of the neck of the first rib, and may extend to the seventh cervical (C7) vertebral body [1]. The stellate ganglion block (SGB) is an accepted intervention for the treatment of a variety of pain conditions of the head and neck regions as well as the upper limbs [2]. SGB is also effective in the treatment of phantom pain, postherpetic neuralgia, cancer pain, cardiac arrhythmias, orofacial pain, and vascular headache [3].

SGB is conventionally performed using a blind technique. However, this blind technique can cause various adverse effects, such as inadvertent epidural, subarachnoid, or intravascular injection, formation of haematomas, and oesophageal injury [4–6]. Ultrasound-guided SGB was introduced in 1995 [7]. Ultrasound scanning can allow for imaging and distinction of the anatomical structure of the neck. Ultrasound-guided SGB is safer than the conventional technique and allows the use of a small injectate volume while maintaining the same degree of efficacy.

SGB leads to vasodilation of the head and neck. However, controversy remains regarding the changes in cerebral and extracerebral blood flow in the head. Liu et al. [8] reported that the blood flow velocities of the internal carotid artery (ICA) on the ischaemic side were decreased and the resistance indexes were increased in 12 patients with ischaemic optic neuropathy (ION) after daily SGB treatment on the affected side with 2–3 mL of 2% lidocaine, for a treatment period of 10–15 days. In contrast, the blood flow velocities of the ICA on the ischaemic side were increased and the resistance indexes were decreased. Ohinata et al. [9] reported that patients who underwent SGB experience increased blood flow of the common carotid artery (CCA) and vertebral artery (VA) on the side of the SGB and decreased blood flow on the opposite side. Nitahara et al. [10] showed that SGBs with 6–8 mL of 1% mepivacaine can significantly increase the blood flow velocity in the CCA, whereas velocity in the VA was unchanged. On the side contralateral to the SGB, significant changes in blood flow velocity in the CCA and VA were never observed. SGB can increase blood flow in the anastomotic artery after superficial temporal artery-middle cerebral artery bypass [11]. In patients with subarachnoid haemorrhage (SAH) after SGB, a significant increase in the calibre of the middle cerebral artery (MCA), VA, and arteriae basilaris (BA) was observed. It has also been shown that the calibre of the MCA, VA, and BA was increased in patients without SAH after treatment with SGB [12].

Kapral et al. [7] and Narouze et al. [13] reported a successful treatment effect with 5 mL of local anaesthetic in ultrasound-guided SGB. Two studies reported on the optimal volume of local anaesthetic required for successful ultrasound-guided SGB compared to the traditional approach [14, 15]. One study showed that 4 ml of 0.2% ropivacaine was sufficient for a successful block [14], while the other showed the optimal volume was 2 ml of 0.5% mepivacaine [15].

Therefore, there is no strong evidence regarding the effect of SGB on the blood flow of the CCA and VA. The blocking effect may be different due to the different anaesthetic drugs, the different volume, or the number of treatments used in SGB. Our aim was to design and conduct a double-blind, randomized controlled crossover trial to evaluate the effects of ultrasound-guided SGB on the CCA and VA in subjects with primary headaches. We chose to use 6 ml 1% lidocaine to perform the SGB because lidocaine is safe and this injection volume can reliably ensure the success of SGB.

### Objective

We designed this prospective, double-blinded, controlled crossover study to investigate the cervical blood flow changes after SGB. The peak systolic velocity (PSV), the end diastolic velocity (EDV), diameter, and resistance index (RI) of the CCA and VA will be measured before and 15 min after each procedure. The rate of ptosis, conjunctival flushing, and the pain scores will also be recorded.

### Trial design

A double-blinded, randomized controlled crossover trial will be conducted, and all subjects will undergo ultrasound-guided SBG. Group A will first undergo SGB with 6 ml 1% lidocaine. After a one-week washout period, this group will receive ultrasound-guided SGB with 6 ml normal saline. In contrast, group B will receive the opposite protocol. That is, group B subjects will first receive SGB with 6 ml normal saline, and after a one-week washout period, this group will receive SGB with 6 ml 1% lidocaine.

## Methods

### Setting

This trial is a prospective, investigator and observer-blinded, randomized, crossover trial. This study will be carried out in the Shanghai Jiao Tong University Affiliated Sixth People’s Hospital. A flow diagram outlining the trial is provided in Fig. 1. This protocol was designed in accordance with the Standard Protocol Items: Recommendations for Interventional Trials (SPIRIT) guidelines [16], which can be found in Additional file 1. Adherence reminder meetings will take place before the beginning of the study. Every team member and research physician will be informed of the importance of the trial procedures and flow.

**Fig. 1 Fig1:**
[figure not shown]
Participant flow diagram according to Consolidated Standards of Reporting Trials (CONSORT)

### Recruitment

Recruitment for this study began on 11 June 2017. The trial is currently actively recruiting from Shanghai Jiao Tong University Affiliated Sixth People’s Hospital, China. Eligible participants are identified and approached in the pain management centre. The patient’s consent to participate in the trial will be obtained prior to any trial-related procedures. Consent will be obtained by an appropriately trained research delegate. Patients will be asked whether they consent to the storage of their contact details so that a qualitative researcher may invite them to participate in a qualitative interview about views on SGB treatment. The qualitative researcher will collect consent for participation in this additional interview immediately prior to commencement of the interview using the qualitative interview Consent Form.

### Inclusion criteria

Participants who meet the diagnostic criteria for primary headaches [17] will be included if they are aged between 18 and 70 years and have signed an informed consent form.

### Exclusion criteria

Participants who meet any of the following criteria are not eligible for this study:Participants with a space-occupying lesionKnown chronic liver or kidney diseaseParticipants with coagulation disordersParticipants with systemic or local infectionParticipants with drug allergiesPsychotic patients

### Dropout criteria

Participants will be withdrawn from the study if they are not willing to continue their participation, cannot be present on the day of the experiment, or miss a treatment session and/or change their form of rehabilitation during the study.

### Intervention

All participants will undergo two SGBs, with a one-week washout period between them. For the ultrasound-guided SGB, each patient will receive 6 mL 1% lidocaine and 6 mL normal saline at one-week intervals to allow a washout period for the injection. The 1% lidocaine is composed of 2% lidocaine and normal saline in a 1:1 ratio (for example, the 1% lidocaine 2 mL is prepared by combining 2% lidocaine 1 mL, and normal saline 1 mL) [18, 19].

The patients will be positioned in a supine position with their neck slightly hyperextended. Prior to the procedure, the C7 level is confirmed by the use of a 7–14 MHz linear probe (S-Nerve, Sonosite, USA). On the short-axis view, the posterior tubercle and the vertebral body show as a slope in the transverse process of C7. Sonoanatomy of the neck at the C7 level is confirmed by the absence of the anterior tubercle. The thyroid, inferior thyroid artery, oesophagus, internal jugular vein, CCA, VA, and prevertebral fascia are also confirmed. Colour Doppler imaging is utilised to avoid penetrating the CCA, VA, and the internal jugular vein during the needle insertion. The neck area will be sterilised and the probe will be covered with sterilised vinyl. At the C7 level, the probe will be placed at the anterior scalene muscle, which is located between the carotid sheath and the brachial plexus. A 25-gauge, 6-cm needle will be inserted laterally, 5 mm from the probe. The needle tip is placed posterior to the carotid artery and anterior to the longus colli muscle under the transverse short axis for the in-plane approach. The assigned dosage of 1% lidocaine or normal saline will be injected in the patients.

At the end of the SGB, another doctor, who is not involved in the operation, will observe the ptosis and conjunctival flushing. Before and 15 min after the SGB, the flow measurements will be recorded by an ultrasound specialist. Sonograms will be obtained with a Mylab 90 (Genova, Italy) by using a linear probe (curved-array transducer, CA431, 1–8 MHz).

### Expected risks

The most serious complications of SGB include intravascular injections and retropharyngeal haematoma. The proximity of the stellate ganglion to the inferior thyroid, vertebral, or carotid arteries provides the potential for intravascular injection or vascular trauma, with resulting bleeding and haematoma [20]. Intravascular injection of even small volumes of local anaesthetic may result in loss of consciousness, apnoea, and seizure [21]. Retropharyngeal haematoma varies in severity, from mild and asymptomatic to severe and life-threatening, causing tracheal compression requiring emergency tracheotomy [22, 23]. The frequency of catastrophic retropharyngeal haematoma after SGB, with resulting airway compromise and obstruction, has been estimated as 1 in 100,000 cases [23]. Compared with the blind technique, however, ultrasound-guided SGB significantly reduced the incidence of asymptomatic haematoma [7].

Ultrasound-guided SGB, with direct visualisation of the multiple vulnerable soft tissue structures enclosed in a tight vascular space around the sympathetic chain, appears to be safer than traditional approaches. To avoid adverse risks to the patients, we will use ultrasound guidance to carefully distinguish the cervical spine, vessels, soft tissue, and trachea. We will also monitor the path and the depth of the needle in real time during ultrasound-guided SGB.

### Expected benefits

Ultrasound-guided SGB may alleviate pain in patients with primary headaches, and it may also contribute to an improved quality of life. Moreover, these participants will play an important role in correctly understanding vascular changes caused by SGB and will contribute to the scientific knowledge on the use of SGB.

### Outcomes

#### Primary outcomes

To evaluate the effect of SGB on the vascular blood flow in the neck, the primary outcomes will be the peak systolic velocity (PSV), the end diastolic velocity (EDV), diameter, and resistance index (RI) of the CCA and VA at 15 min after the first SGB (T1). Sonograms will be obtained with a Mylab 90 (Genova, Italy) by using a 4–10-MHz linear transducer. For flow-volume measurements, a straight segment of the common carotid artery at least 2 cm below the carotid bulb will be selected [24].

All measurements will be performed by an ultrasound specialist using the same ultrasound instrument.

